### Non-investigational medical products

In this trial, it is medically necessary in most cases for clinical trial subjects to receive a multi-drug immunosuppressive regimen to prevent allograft rejection. Therefore, in addition to IMP, patients will be treated with a therapy of several other immunosuppressive agents, regardless of randomisation group. All systemic immunosuppressive therapy given will be collected in the eCRF.

The following substances are prohibited during study participation:CyclosporineAny tacrolimus preparation other than the assigned IMP (excluding immediate-release formulations taken prior to randomisation or during an acute rejection episode or in place of the IMP during a temporary interruption of IMP)St. John’s wort (*Hypericum perforatum*)Grapefruit and grapefruit juice

## Data collection methods

### Run-in phase (optional)

The optional run-in phase starts immediately after organ transplantation surgery. During this phase, LTx recipients can be screened for inclusion in the EnGraft Study and may receive immunosuppression and concomitant medication as per local standard practice.

The following procedures will take place:Signed informed consentEvaluation of patient eligibility including, if applicable, pregnancy testMeasurement of tacrolimus trough levels (if patient treated with an oral formulation of immediate-release tacrolimus)Testing for donor-specific antibodies (if per local practice)

### Visit 1—Baseline

At the baseline visit (visit 1), patients are randomised and baseline characteristics are measured. The date of the baseline visit is designated as trial “day 0” and must occur no later than 14 days after transplantation surgery.

In case the run-in phase is skipped, all screening procedures must be performed at the baseline visit prior to randomisation. Randomisation may take place only after all eligibility criteria have been checked and fulfilled.

The following baseline procedures/data will be performed/collected (the applicable panel of assessments is displayed in Fig. 4):Randomisation, dispensing of assigned IMP, explaining practicalities of drug administration to the patientPatient characteristics, including demographicsPast medical historyDonor and transplantation dataPhysical examination, including body weight12-lead ECGVital signs: blood pressure, pulse rate, body temperatureBlood sampling for clinical tests:◦ Haematology, serum biochemistry, including calculation of eGFR◦ Blood coagulation screen◦ Virology status: CMV, EBV, HCV, HBV◦ Tacrolimus trough level (if immediate-release tacrolimus given prior to randomisation)Urine sampling for clinical urine analysisReview and documentation of concomitant medication that interacts with IMP or is prohibited per protocol

**Fig. 4 Fig4:**
[figure not shown]
Schedule of clinical assessments

### Visit 2 to visit 6 (day 3 to day 28) of controlled treatment phase

During the first 4 weeks after randomisation, five study visits are performed and assessments should be conducted according to Fig. 4. Tacrolimus trough level measurements should be performed (at least) according to the minimum scheduled outlined in Fig. 3. A time window of ± 1 day is permitted for visits 2–4, this time window extends to ± 2 and ± 3 days for visit 5 and visit 6, respectively.

At visit 6, the patient should be assessed for signs of de novo occurrence of tremor or vision impairments. If detected, these should be documented as adverse events.

### Visit 7 (day 84 ± 7 days) of controlled treatment phase

The applicable panel of assessments at visit 7 is displayed in Fig. 4, including an optional donor-specific antibody (DSA) test and an optional fibroscan/protocol biopsy. Visit 7 marks the 12-week time point that will be used to evaluate the primary endpoint (tacrolimus C/D ratio), which will be calculated using the trough level measured in the blood sample collected on the day of visit 7 (12 weeks) and the dose of study drug taken by the patient one day prior to visit 7. To standardise measurement of the visit 7 trough level across all participating study sites, an additional aliquot of EDTA-blood will be collected and shipped to the University Hospital Regensburg for central analysis.

### Visit 8 to visit 10 (year 1 to year 3 ± 21 days) of follow-up phase

The follow-up visits will take place annually until year 3, i.e. visit 8 (1 year after randomisation), visit 9 (2 years after randomisation) and visit 10 (3 years after randomisation).

The panel of assessments for the follow-up visits is shown in Fig. 4.

### Sample size calculation

Sample size estimation is based on testing superiority of Envarsus® versus Advagraf™ with respect to the primary efficacy variable. C/D ratio data obtained from previously published clinical trials in kidney transplantation and observational studies in LTx inform an assumed difference between the two treatments Envarsus® or Advagraf™ after 12 weeks of approximately 0.4 with a standard deviation of 1.0.

A sample size of 100 patients per treatment group will have the power of 80% to show a difference of 0.4 in C/D ratio between the two treatment groups with a two-sided significance level of 5%. The primary test will be performed based on the Full Analysis Set (FAS) but will be repeated for the Per-protocol analysis set (PPAS). To have a sufficient power also for the PPAS comparison, it is planned to randomise 134 patients in each treatment group assuming that about 25% of randomised patients cannot be included in the PPAS because of major protocol deviations. A sample size of 134 patients per treatment group will have a 90% power to show a difference of 0.4 in C/D ratio in the FAS. The minimal detectable difference in the FAS will be 0.24.

### Hypotheses

The following null (H_0_) and alternative (H_a_) hypotheses will be tested for the primary endpoint (C/D ratio) at a two-sided significance level of α = 0.05:$${H}_{0}: {\mathrm{Mean}}_{\mathrm{Envarsus}}= {\mathrm{Mean}}_{\mathrm{Advagraf}} , \mathrm{versus}$$$${H}_{\mathrm{a}}: {\mathrm{Mean}}_{\mathrm{Envarsus}} \ne {\mathrm{Mean}}_{\mathrm{Advagraf}}$$in which Mean _Envarsus_ and Mean _Advagraf_ refer to mean C/D ratio at visit 7 (12 weeks after randomisation) in the Envarsus® and Advagraf™ treatment groups, respectively.

### Population for analysis

The primary analysis will be based on the FAS. However, a sensitivity analysis will be done on the PPAS. All safety data will be analysed by means of the safety population.

### Full Analysis Set (FAS)

This consists of all randomised trial patients with at least one tacrolimus blood trough level reading after randomisation.

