A new once-daily formulation of tacrolimus, Envarsus®, was approved in 2014 by the European Medicines Agency (EMA) for the prophylaxis of rejection in kidney or liver allograft recipients and treatment of rejection resistant to other immunosuppressants [11]. Envarsus® is a prolonged-release formulation of tacrolimus developed using MeltDose™ drug-delivery technology, which increases the bioavailability of poorly water-soluble compounds via solid formulation at molecular state. Improvement in the bioavailability of Envarsus®, which allows once-daily administration, results in lower inter- and intra-patient variability of drug absorption with reduced peak-to-trough fluctuation and earlier achievement of a stable tacrolimus profile, as demonstrated in healthy volunteers [12]. In phase III studies using stable, de novo kidney transplant patients, Envarsus® has proven to be non-inferior to twice-daily tacrolimus in terms of treatment failure, a composite trial endpoint of death, graft failure, acute rejection or lost-to-follow-up [13, 14]. Additional potential benefits of Envarsus® are reduced pill burden and diminished peak-related toxicities such as tremor [15].

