## Study design

EnGraft is a prospective, randomised, controlled, multicentre, open-label, two-arm, parallel-group, phase IV clinical trial to assess bioavailability and practicability of *En*varsus® compared with Adva*graf*™ in de novo liver *t*ransplant recipients (EnGraft).

Two hundred and sixty eight (268) patients at 15 LTx centres in Germany will be enrolled and randomised in a 1:1 ratio to two study arms. Patients in the test arm will be treated with Envarsus® (test) as first-line CNI in the immunosuppressive regimen. The control arm will treat patients with Advagraf™ (comparator) as first-line CNI. Trial participants will additionally receive all of the other treatments that comprise a standard, multi-drug, immunosuppressive regimen for LTx recipients, according to routine clinical practice in Germany.

Since this trial compares two commercially available medications with different pharmaceutical formulations (Envarsus® tablets versus Advagraf™ capsules), simple, cost-neutral treatment blinding is not possible. The trial is being conducted as an open-label study.

LTx will be performed prior to study entry, according to the local standard at participating trial centres. An optional run-in phase is available, in case patients cannot be randomised immediately after transplantation surgery (e.g. unable to swallow study medication). Patients may be enrolled up to 14 days after surgery.

The day of randomisation to EnGraft is defined as trial day 0. After a 12-week controlled treatment phase, patients enter a follow-up phase of 2 years and 9 months. The final study visit is scheduled for 3 years after randomisation.

The study design adheres to the principles outlined in ICH-GCP E6 (R2). All patients aged ≥ 18 years who meet the eligibility criteria and give informed consent will be allocated to the study. Those patients are supplied with patient information. For each trial participant, an authorised and delegated trial investigator must obtain written informed consent after sufficient time for reflection prior to conducting any trial-related procedures involving the subject. After consent is obtained, patients are randomised to the trial. The used patient information sheet and the informed consent are both ethically approved (Fig. 1).

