### Safety population

This consists of all trial patients who receive at least one dose of study IMP after randomisation. The safety population will be used for analysis of all safety variables.

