### Statistical analysis

The statistical analysis will be done by Excelya Germany GmbH. All statistical analyses will be carried out using SAS® 9.4 or higher.

For efficacy and PK endpoints, all patients will be analysed as belonging to their randomised IMP, regardless whether patients received a treatment different from the treatment to which they were randomised. For safety endpoints, all patients will be analysed according to the treatment they actually received.

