### Primary endpoint

The aim of the EnGraft Study is to show that Envarsus® is superior to Advagraf™ with respect to the primary variable, which is defined as the C/D ratio at week 12 after randomisation.

The analysis of the primary endpoint will be performed by means of analysis of covariance considering randomised treatment and pre-treatment with immediate-release tacrolimus (stratification factor) as fixed effects in the model. Least square means, standard errors, treatment difference and corresponding 95% confidence intervals will be reported.

The primary population for analysis of the primary endpoint, secondary efficacy endpoints and secondary pharmacokinetic endpoints will be the FAS. Supportive analyses will be carried out for the PPAS.

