### Missing data

A multiple imputation approach will be used to account for missing values of the primary variable at week 12.

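### Randomised patients who never have a post-randomisation trough fall out of the Full Analysis Set, which appears to be the set for death, graft failure and rejection (minor)

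*Protocol article*

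**What the plan says.** The section Full Analysis Set (FAS) limits the set to "all randomised trial patients with at least one tacrolimus blood trough level reading after randomisation". It gives no deadline for that reading and does not tie it to the assigned product.

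Under Statistical analysis, the Primary endpoint section assigns the set: "The primary population for analysis of the primary endpoint, secondary efficacy endpoints and secondary pharmacokinetic endpoints will be the FAS".

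Selected secondary endpoints lists biopsy-proven rejection, graft failure and death, each at 12 weeks and at 1, 2 and 3 years. It does not label any of them as efficacy or safety.

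The Safety population is "all trial patients who receive at least one dose of study IMP after randomisation". The Statistical analysis section says that for efficacy and PK endpoints "all patients will be analysed as belonging to their randomised IMP", while safety endpoints follow the treatment actually received. The article names no set of all randomised patients.

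Two further statements bear on the point. Study design says "The trial is being conducted as an open-label study". Missing data says "A multiple imputation approach will be used to account for missing values of the primary variable at week 12", and no such provision is given for the clinical events.

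**The concern.** Membership of the FAS depends on something that happens after randomisation, when the allocation is already known to patient and investigator. For trough and dose endpoints that is natural, because a patient without a reading has nothing to summarise. For death, graft failure and rejection it is not: these can be established without a drug level. A patient excluded for want of a trough is excluded from every later time point as well, up to year 3.

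At stake is the randomised comparison of the clinical events. The Rationale wants to show a benefit for the kidney with no penalty for graft survival, and that reassurance rests on small event counts. In an open-label trial the reasons for never having a trough could differ between arms.

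**Working it through.** **1. Who is in which set.** Applying the definitions as written:

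| Randomised patient | FAS | Safety population |
|---|---|---|
| Rejection or re-transplantation before the first trough, any tacrolimus level read later | in | in, if dosed |
| Dosed, dies or withdraws before any trough | out | in, by treatment received |
| Dosed, tacrolimus stopped for good before any reading | out | in, by treatment received |
| Neither dosed nor a trough | out | out |

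Only the last three rows leave the FAS, and only the last row leaves both sets. Neither set is everyone randomised.

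**2. The plan's own figures.** Inputs from Sample size calculation: difference 0.4, SD 1.0, two-sided 5%, 80% power, 25% loss from the per-protocol set.

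- n per group = 2 × (1.960 + 0.842)² × 1.0² / 0.4² = 98.1, so 99 (99.1 by the t-test). The plan uses 100.
- 100 / 0.75 = 133.3, so 134 per group, 268 in total.
- Power with 134 per group: standard error √(2/134) = 0.1222; 0.4/0.1222 − 1.960 = 1.314, which gives 90.6%. The plan states 90%.
- Smallest significant difference: 1.960 × 0.1222 = 0.239. The plan states 0.24.

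All figures reproduce. The stated FAS power uses all 134 per group, so it allows no loss from the trough condition.

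**3. Effect on the primary endpoint.** The loss is not given. The shares below are assumptions, spread evenly over the arms.

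| Assumed loss | Patients of 268 | Power |
|---|---|---|
| 0% | 0 | 90.6% |
| 1% | 2.7 | 90.3% |
| 2% | 5.4 | 90.0% |
| 3% | 8.0 | 89.7% |
| 5% | 13.4 | 89.1% |

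**4. How many very early deaths to expect.** The first visit after randomisation is at day 3, with a window of one day either way. The figure with the trough schedule is not available here, so the first trough may come sooner. The Background gives one-year patient survival of about 85%. Assuming a constant hazard from randomisation, h = −ln(0.85)/365 = 0.000445 per day, and expected deaths by day d are 268 × (1 − exp(−h × d)).

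- Day 3: 0.36. Day 4: 0.48. Day 7: 0.83. Day 84: 9.8.
- By day 4 this is about 0.24 per arm and 0.48/9.8 = 5% of the 12-week deaths.

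The true hazard soon after transplantation is probably higher, and the early count rises roughly in proportion. Immediate withdrawals come on top, and the documents give no rate for them. An assumed range of 0 to 8 excluded patients (up to 3% of 268) is generous.

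**5. What one excluded death does.** Assume 5 later deaths per arm by week 12 (step 4 gives 9.8/2 = 4.9) and one further death before any trough in one arm.

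- All randomised: 6/134 = 4.48% against 5/134 = 3.73%, a difference of 0.75 percentage points.
- FAS: 5/133 = 3.76% against 3.73%, a difference of 0.03 points.

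One such death moves the arm's figure by 4.48 − 3.76 = 0.72 points.

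**The case against.** The strongest reply is that almost nobody is affected. One trough at any time is enough. A reader might infer that rejection or graft loss before the first reading disappears from the analysis. The definition does not support that, because any later tacrolimus level brings the patient in and the event counts. The article expects such levels: the section on non-investigational products allows immediate-release tacrolimus during an acute rejection or an interruption of the study drug, and the section on cross-over asks for a return to the assigned product.

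Second, it is an inference that these events belong to the FAS. The article describes "a composite trial endpoint of death, graft failure, acute rejection or lost-to-follow-up" as the treatment-failure endpoint of earlier kidney trials, which suggests an efficacy reading but does not classify the endpoints of this trial. This stands as a limit. It does not remove the point, because the safety population is not everyone randomised either.

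Third, a patient who was dosed and died before a trough remains in the safety population, and all adverse events are recorded. That also stands: such a death would still be reported, though not in the FAS comparison.

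Fourth, under Secondary endpoints these variables are descriptive, and any tests are exploratory. No confirmatory conclusion depends on them.

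What is left is a definition that ties events needing no trough to having one, with no set in the article that contains all randomised patients.

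**Conclusion.** The point holds and is minor. The FAS leaves out randomised patients who never have a trough, chiefly very early deaths and immediate withdrawals. The clinical event endpoints appear to be analysed in it. The safety population does not make good the all-randomised comparison.

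The size is unknown but probably small: well under one expected death by day 4 under a constant hazard from 85% one-year survival, plus an unstated number of withdrawals. One excluded death would shift an arm's 12-week mortality by about 0.7 percentage points, if 5 later deaths per arm are assumed.

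A reader might go on to infer that mortality will be materially understated or that the arms will be biased. The documents give no count of patients without a trough and no sign that it differs by arm, so neither can be claimed. Nor is the primary analysis in doubt. Imputation makes the trough condition dispensable there, but a patient with no reading adds almost no information, and power stays at about 90% for any plausible loss.

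**What to change.** - State that death, graft failure and biopsy-proven rejection are analysed in all randomised patients, in the arm to which they were randomised, using whatever follow-up is available.
- Keep the condition of at least one trough for the trough, dose and C/D endpoints.
- Report the number of patients without a post-randomisation trough by arm, with reasons, and say for each clinical endpoint which set applies.

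The cost is a sentence or two in the protocol or SAP and one line in the patient flow. Patients who stay in follow-up need no new data collection. The downside is that patients who withdraw at once may have unknown event status. Redefining the set does not recover it, so it has to be shown as missing by arm and not counted as event-free.

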### Per-protocol analysis set (PPAS)

This consists of the FAS without any major protocol deviations (e.g. violation of eligibility, non-/poor compliance, non-permitted medications). The precise definition of the PPAS will be specified by the sponsor after review of aggregated data without information on individual treatment assignment, prior to database lock for the primary analysis.

### Safety population

This consists of all trial patients who receive at least one dose of study IMP after randomisation. The safety population will be used for analysis of all safety variables.

### Statistical analysis

The statistical analysis will be done by Excelya Germany GmbH. All statistical analyses will be carried out using SAS® 9.4 or higher.

For efficacy and PK endpoints, all patients will be analysed as belonging to their randomised IMP, regardless whether patients received a treatment different from the treatment to which they were randomised. For safety endpoints, all patients will be analysed according to the treatment they actually received.

### Patient demographics and baseline characteristics

Demographics and baseline characteristics/assessments will be summarised in total and by treatment arm using descriptive statistics.

The following variables will be summarised: age, gender, race, BMI, medical history, physical examination, vital signs, 12-lead ECG, laboratory data and donor characteristics.

### Primary endpoint

The aim of the EnGraft Study is to show that Envarsus® is superior to Advagraf™ with respect to the primary variable, which is defined as the C/D ratio at week 12 after randomisation.

The analysis of the primary endpoint will be performed by means of analysis of covariance considering randomised treatment and pre-treatment with immediate-release tacrolimus (stratification factor) as fixed effects in the model. Least square means, standard errors, treatment difference and corresponding 95% confidence intervals will be reported.

The primary population for analysis of the primary endpoint, secondary efficacy endpoints and secondary pharmacokinetic endpoints will be the FAS. Supportive analyses will be carried out for the PPAS.

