## Interventions

### Randomisation

A dynamic allocation technique will be used for randomisation of patients fulfilling the trial eligibility criteria in a 1:1 ratio to one of two treatment arms: Envarsus® tablets (test IMP) or Advagraf™ capsules (comparator IMP). Pre-treatment with immediate-release tacrolimus (Yes/No), as well as trial site, will be used as stratification factors in the treatment allocation to minimise sources of treatment bias. The first stratification factor (study centre) will minimise systematic treatment bias at the study centre level and reduce the influence of inter-centre variability. The second stratification factor (pre-treatment with immediate-release tacrolimus) will minimise treatment bias at the level of the individual patient, since patients treated with Prograf® during the run-in phase can be expected to develop stable trough levels after randomisation more rapidly than patients who do not receive Prograf® prior to commencing IMP. Balancing the treatment arms with respect to this factor allows fair and unbiased evaluation of the secondary pharmacokinetic endpoints that evaluate the ease with which the first target trough level is achieved.

The allocation algorithm is programmed into a randomisation module in the trial database. Study investigators at the participating trial sites have access to the randomisation module via the online trial database and randomise using this central tool. It is vital that randomisation is performed as soon as possible after eligibility has been confirmed and no later than 14 days after transplantation surgery; enrolment after this time period is not allowed.

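### Allocation is balanced on trial site, but the primary model leaves site out, so the test is mildly conservative if sites differ in C/D ratio

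*Protocol article*

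**What the plan says.** Protocol article, Randomisation: "A dynamic allocation technique will be used for randomisation of patients fulfilling the trial eligibility criteria in a 1:1 ratio". The same section names the balancing factors: "Pre-treatment with immediate-release tacrolimus (Yes/No), as well as trial site, will be used as stratification factors in the treatment allocation". It also says why centre is one of them: balancing on it "will minimise systematic treatment bias at the study centre level and reduce the influence of inter-centre variability".

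Protocol article, Statistical analysis, Primary endpoint: the C/D ratio at week 12 is compared by "analysis of covariance considering randomised treatment and pre-treatment with immediate-release tacrolimus (stratification factor) as fixed effects in the model". Pre-treatment is the only allocation factor carried into this model. Nothing elsewhere in the article brings site back as a fixed effect, a random effect or a sensitivity analysis, and no reason is given for leaving it out.

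Scale of the trial, from Study design: "Two hundred and sixty eight (268) patients at 15 LTx centres in Germany will be enrolled and randomised in a 1:1 ratio".

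**The concern.** When allocation forces the arms to be similar within each site, a site with high or low C/D ratios contributes almost equally to both arms, and its effect largely cancels from the treatment difference. The true sampling variance of that difference then reflects mainly within-site variation. An analysis without site estimates its residual from total variation, between-site part included. It therefore reports a standard error for a less precise design than the one actually run.

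At stake is efficiency. The protocol balances on centre to limit the influence of differences between centres, yet that gain does not reach the reported standard error, confidence interval or p-value. Because the article spells out the model terms and includes one balancing factor without the other, this is a stated choice and not merely a detail left to the analysis plan.

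**Working it through.** **Inputs**
- From Sample size calculation: an assumed difference "after 12 weeks of approximately 0.4 with a standard deviation of 1.0", and 100 per arm, which "will have the power of 80% to show a difference of 0.4 in C/D ratio between the two treatment groups"; 134 per arm after allowing for 25% exclusions from the per-protocol set; 90% power in the full analysis set; minimal detectable difference 0.24; two-sided 5% level.
- From Study design: 15 sites, 268 patients.
- Not in the document, so assumed: the share of total C/D variance that lies between sites (ICC), taken as 5%, 10% and 15%. The SD of 1.0 is treated as the total SD.

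**Step 1. The plan's own figures reproduce.** The normal approximation needs 99 per arm for 80% power, and 100 per arm gives 80.7%. 100 / (1 − 0.25) = 133.3, rounded up to 134. Power at 134 per arm is 90.6% (90.4% with the t distribution). The smallest difference reaching significance is 1.96 × √(2/134) = 0.239. The sample size is not in question.

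**Step 2. Effect of omitting site, with perfect balance within sites.**
- Reported SE (site omitted) = √(2/134) = 0.1222
- True SE = √(2(1 − ICC)/134)
- Overstatement = 1/√(1 − ICC) − 1
- True two-sided alpha = 2 × [1 − Φ(1.96/√(1 − ICC))]
- With λ = 0.4/0.1222 = 3.274: power without site = Φ((λ − 1.96)/√(1 − ICC)); power with site = Φ(λ/√(1 − ICC) − 1.96)

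| Assumed ICC | True SE | SE overstated by | True alpha | Power without site | Power with site | Power forgone (points) |
|---|---|---|---|---|---|---|
| 0 | 0.1222 | 0% | 5.0% | 90.6% | 90.6% | 0 |
| 5% | 0.1191 | 2.6% | 4.4% | 91.1% | 91.9% | 0.8 |
| 10% | 0.1159 | 5.4% | 3.9% | 91.7% | 93.2% | 1.5 |
| 15% | 0.1126 | 8.5% | 3.4% | 92.3% | 94.4% | 2.1 |

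**Step 3. Approximate balance.** A dynamic allocation balances sites only approximately, so Step 2 gives upper limits. A simulation used 15 unequal sites, 268 patients, minimisation on site and pre-treatment with a biased coin of 0.85, and 3000 runs per setting. The site sizes and the coin are assumptions.
- ICC 5%, site omitted: mean reported SE 0.1218 against empirical SE 0.1192, an overstatement of 2.2%; alpha 0.043.
- ICC 10%, site omitted: 0.1215 against 0.1171, an overstatement of 3.8%; alpha 0.045.
- ICC 10%, site included: reported 0.1162 against empirical 0.1166; alpha 0.053.
- ICC 0: including site raises the mean reported SE only from 0.1219 to 0.1224.
- Simple randomisation, ICC 20%, site omitted: alpha 0.051. The conservatism therefore comes from balancing on site and then omitting it.

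The Monte Carlo error of each alpha is about 0.004. The ICC 0 run gave 0.059 without site and 0.058 with it, so small differences between simulated alphas should not be over-read.

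**The case against.** The strongest reply is that nothing is broken. The estimate is unbiased, the error rate is at or below 5%, and even without site every power figure above exceeds the stated 90%. All of that stands, and it sets the grade of this point.

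The effect may also be small. The week-12 trough is measured centrally, which removes laboratory differences between sites, and week 12 was chosen because metabolism should be stable and the influence of concomitant immunosuppressants weaker by then. With no between-site variance there is no effect at all. This stands as a limit on the size. It does not show that site variance is zero: background immunosuppression follows routine practice, run-in treatment follows local practice, investigators set the individual target ranges, and the protocol's own reason for balancing on centre presumes that centres vary.

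Site is not costless to include either. 268/15 is about 18 patients per site, and some sites may be much smaller, so a random effect or a pooling rule is needed. The full analysis plan is not shown and may already deal with this; the published model does not.

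A reader might infer that the primary test is invalid, that type I error is inflated or that the trial is underpowered. The documents support none of these: the error runs in the conservative direction, and the planned power holds with SD 1.0 as the total. A reader might also infer that body weight belongs in the model because starting doses are per kg. Weight is not an allocation factor, so the mismatch argument does not reach it, and the documents give no basis for sizing a gain.

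**Conclusion.** The point holds as a minor efficiency improvement. The primary model carries one of the two factors used to balance allocation. If site explains 5% to 15% of the variance in the 12-week C/D ratio, the reported standard error is at most about 3% to 9% too large, and less under approximate balance. The true two-sided error rate is then about 3.4% to 4.5%, and about 1 to 2 points of power are given up. These sizes rest on an assumed ICC, a total SD of 1.0 and, at the upper limits, perfect balance within sites. The direction rests only on site variance being above zero. A positive superiority result from the model as written would still be valid.

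**What to change.** Before database lock, define the primary model as randomised treatment, pre-treatment (Yes/No) and trial site. Fit site as a random intercept, or as a fixed effect with a rule, written in advance, for pooling very small sites. If site is to stay out, state the reason.

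The cost is one sentence and no new data. With site fixed, at most 15 − 1 = 14 of the 268 − 3 = 265 residual degrees of freedom are used, leaving 251; a random intercept uses fewer. The sample size does not change.
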